#### 10.2.4. Data Types, Processing, and Analysis

Stage 1. The participants’ age, gender, marital status, education and current occupation, and their intention to be vaccinated against COVID-19 (or receive booster doses), will be assessed using the WHO SAGE 10-item Vaccine Hesitancy Scale and the 4-Item Vaccine Confidence Index, for which valid and reliable versions are available in Chinese (both Mandarin and Cantonese) and English. After the first wave of surveys has been completed, 20–3 respondents will be selected using stratified sampling to achieve a representative sample with respect to age, gender, cultural/ethnic background and economic background, in that order. These participants will be invited to attend an online in-depth qualitative interview to explore their reasons for vaccine hesitancy and thoughts/concerns in relation to COVID-19 vaccines as identified in the initial cross-sectional survey. More participants will be approached for interviewing until data saturation is reached. All of the survey instruments will be scored according to the published guidelines and summarised using descriptive statistics, and univariate analysis will be performed to compare different vaccine acceptance/hesitancy-related outcomes among respondents with various socio-economic backgrounds. Qualitative content analysis guided by the Vaccine Hesitancy Determinants Matrix Model will be performed to comprehensively analyse the reasons for vaccine hesitancy among the HK population. The video-recorded interviews will be transcribed into text (either in Chinese or English). The data will be content-analysed and coded into categories. Any discrepancy in coding/category will be resolved by discussion, and the final themes/subthemes will be agreed upon by our team. The reflexivity and trustworthiness of the data will be guaranteed through in-depth interviewing techniques, and through rigorous data analysis involving more than three researchers.

Stage 2. Primary outcome: Vaccine hesitancy measured by adult Vaccine Hesitancy Index; Secondary outcome: Vaccine confidence assessed by Vaccine Confidence Index; A question with a ‘Yes/No’ answer will be asked: Have you scheduled a specific date for the next COVID-19 Vaccination? An open-ended question about people’s perception of and behaviour pertaining to COVID-19 vaccines will be asked. We will also assess participants’ perception of their degree of attitudinal change using three one-item measures of readiness for vaccine perception: How important is it for you to receive a COVID-19 vaccine?; How ready are you to receive a COVID-19 vaccine?; and How confident are you about receiving a COVID-19 vaccine? The participants will answer these questions at each follow-up on a discrete 11-point scale from 0 (not important/ready/confident at all) to 10 (highly important/ready/confident). Outcomes will be assessed at pre-, post-, 3- and 6-month follow up, and booster sessions will be provided every three months to further enhance their motivation for COVID-19 vaccine uptake throughout the study period. Data Analysis: All quantitative data from the pre-and post-tests will be numerically coded, summarised (with descriptive statistics), and analysed. The generalised estimating equation will be used to analyse the effects of the intervention. A tracking system will be implemented to examine the participants’ compliance in using the programme, e.g., the number of views and duration of time spent engaging with the programme. After the first follow-up assessment, selected participants (those with or without improvements in the study outcomes) will be invited for an in-depth qualitative interview to explore their thoughts on the strengths and limitations of the Web-based psychoeducation programme tested in the RCT and will be asked a set of questions assessing the usability of the programme. Any further amendments to the intervention and research procedures will be made based on the feedback from the participants’ interviews. The knowledge base of the programme and its technical foundation will be continuously consolidated and refined during the programme development phase and thereafter when feedback on the programme is available from the participants.

Stage 3. We will not have a control group but will use pre-post designs as our primary focus is the practical implementation of the intervention to a wider population. The statistical analysis methods for effectiveness outcomes of stage 3 will be ANCOVA for continuous variables and Chi-square tests for categorical variables. Our programme ‘AI-driven Vaccine Communicator’ will be disseminated to relevant stakeholders in healthcare settings and the general population to enable its use among a wider population. Considering the likelihood that new COVID-19 vaccines will be developed in response to viral mutations and that the vaccination programme will be expanded to other age/priority groups, our programme will be updated and adapted to sustain its long-term significance and usability.

## 11. Study 5

An educational intervention using a virtual reality game to improve compliance with COVID-19 disease-related hygiene practices and participation in SARS-CoV-2 screening, for the prevention of its transmission between primary schoolchildren in communities: a large-scale stratified cluster RCT.

Given the need to prevent COVID-19 transmission by this age group, an educational VRG should be implemented for primary schoolchildren, to improve their hygiene compliance and increase their awareness of community testing. This study will use a CBPR framework focused on equal participation between the researchers and the community stakeholders being studied (i.e., schools, teachers, schoolchildren and parents).

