### 10.2. Plan of Investigation

#### 10.2.1. Subjects

Our target population will be Hong Kong residents aged ≥18 who show hesitancy toward COVID-19 vaccines. Participants will be defined as COVID-19 vaccine-hesitant if they have no plan for a date to receive the available COVID-19 vaccines in either 1st, 2nd, or 3rd dose [19], or completed three doses of COVID-19 vaccines not based on their willingness and are hesitant for a future 4th dose or regular vaccines).

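### Study 4's Yes/No behavioural item records a pending booking rather than a dose received, and the tests named for Stage 3 do not fit a single-group pre-post design

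*Protocol article*

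**What the plan says.** **Stage 2 (RCT), section 10.2.4.** The primary outcome is the adult Vaccine Hesitancy Index and the labelled secondary is the Vaccine Confidence Index. One Yes/No question follows: "Have you scheduled a specific date for the next COVID-19 Vaccination". There is also an open-ended question, in which people's "perception of and behaviour pertaining to COVID-19 vaccines will be asked", and three 0–10 items on importance, readiness and confidence. Timing: "Outcomes will be assessed at pre-, post-, 3- and 6-month follow up". Booster sessions are given "to further enhance their motivation for COVID-19 vaccine uptake throughout the study period". The intervention effect is to be analysed by generalised estimating equations (GEE).

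**Entry, section 10.2.1.** People count as hesitant "if they have no plan for a date to receive the available COVID-19 vaccines in either 1st, 2nd, or 3rd dose", or if they took three doses unwillingly and are hesitant about later ones.

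**Stage 3 (service evaluation), sections 10.2.3 and 10.2.4.** All participants are contacted again every 3 months about their perceptions and actions on vaccination. The design is stated as "We will not have a control group but will use pre-post designs". The methods for the effectiveness outcomes are "ANCOVA for continuous variables and Chi-square tests for categorical variables".

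**Elsewhere in the article.** Study 1 (section 7.2.3) takes vaccine uptake from the Vaccine Pass or paper certificate, and names McNemar's test for categorical pre-post data.

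**The concern.** The Yes/No item measures a state that ends when the desired behaviour happens. A participant who books a dose, receives it before the 3- or 6-month visit and has no later dose booked truthfully answers No. A participant who has done nothing gives the same answer. Study 4 lists no structured record of doses received and no rule for coding people vaccinated during follow-up. If the programme raises uptake, more participants in the intervention arm move into this ambiguous No, so the arm comparison on the item understates the effect on behaviour.

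In Stage 3 the same people are measured before and after. An ordinary chi-square test treats the two sets of answers as independent samples. ANCOVA normally compares groups adjusted for a covariate, and with a single group there is no group factor through which to estimate the change. At stake are the readability of the one closed behavioural result in the RCT and the efficiency of the Stage 3 tests.

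**Working it through.** **Plan's own figure.** The only computed number nearby is the Stage 2 sample size of 168 (84 per group, 20% attrition). No SD is stated, so 168 cannot be fully re-derived. The attrition step is consistent: 67/0.8 = 83.75, rounded up to 84. Nothing below depends on 168 except that about 84 × 0.8 = 67 completers per arm are used for power.

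**Stage 2 item.** For each arm let v be the proportion vaccinated by the visit, d the proportion not vaccinated but with a date booked, and s the share of the vaccinated who have a further date (taken as equal in both arms).

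- True behaviour (vaccinated or booked) = v + d
- Item Yes rate = d + s·v
- Arm difference on the item = Δd + s·Δv, against a true Δd + Δv

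The uptake part of the effect is therefore multiplied by s. The documents give no value for v, d or s, so all rates here are assumed. Power is Φ[(|Δ| − 1.96·SE₀)/SE₁], with 67 per arm, two-sided 0.05, SE₀ pooled and SE₁ unpooled.

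| Assumed v; d (intervention v control) | s | True v + d | Item Yes | Power, item | Power, v + d |
|---|---|---|---|---|---|
| 30% v 15%; 15% v 10% | 0 | 45% v 25% | 15% v 10% | 0.14 | 0.68 |
| same | 0.5 | 45% v 25% | 30% v 17.5% | 0.40 | 0.68 |
| 40% v 20%; 10% v 10% | 0 | 50% v 30% | 10% v 10% | 0.05 | 0.66 |

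For the second row: 15% + 0.5 × 30% = 30%, and 10% + 0.5 × 15% = 17.5%.

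Reversal needs Δd < −s·Δv. Example: s = 0, 25% v 10% vaccinated, and 15% of the unvaccinated booked in each arm. Then d = 0.75 × 0.15 = 11.25% v 0.90 × 0.15 = 13.5%, so the item shows −2.25 points. The truth is 36.25% v 23.5%, or +12.75 points.

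**Stage 3 chi-square.** With equal margins p and within-person correlation ρ, the variance of the change is 2p(1−p)(1−ρ)/n. The unpaired test uses 2p(1−p)/n. The ratio of standard errors is 1/√(1−ρ), which at ρ = 0.5 is 1/√0.5 = 1.41, or 41% too large.

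A simulation (40,000 runs; assumed 200 participants and 30% Yes before) gives:

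| ρ | Type I error, chi-square | Type I error, McNemar | Power 30%→40%, chi-square | Power 30%→40%, McNemar |
|---|---|---|---|---|
| 0.3 | 0.020 | 0.050 | 0.57 | 0.71 |
| 0.5 | 0.006 | 0.049 | 0.58 | 0.85 |
| 0.6 | 0.002 | 0.050 | 0.58 | 0.92 |

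The error is in the conservative direction.

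**The case against.** **The item mirrors the entry definition.** It asks whether a participant still has no date, which is how hesitancy is defined at entry, and hesitancy is Study 4's target. This stands as a reason to keep the item. It does not make the item a measure of action, because a vaccinated participant with nothing booked would still be classed with those who refuse.

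**It is not the only information on behaviour.** The open-ended question touches on behaviour, and Stage 3 asks about actions. That is correct: the item is the only closed behavioural measure in Stage 2, not the only one of any kind. Free text with no stated coding gives no endpoint that can be compared between arms.

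**Stronger readings of the item.** A reader might infer that everyone vaccinated is counted as No. The documents do not say so: those with a further dose booked answer Yes. A reader might also infer that the item will reverse the trial's result. Reversal needs particular rates, such as those in the example, and no figure in the article supports them. Dilution is the general consequence.

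**Chi-square may mean McNemar.** McNemar's test is a chi-square test, and the article never says unpaired. That reading is possible. But Study 1 names McNemar separately for the same layout, so the ordinary test is the more natural reading here. Likewise, Study 5 mentions repeated-measures analysis of covariance, so an ANCOVA with a time factor might be intended; Study 4 does not say so.

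**Stage 3 is not powered.** Its numbers rest on practical grounds and enrolment is not capped, so lost power matters less. This stands and limits the weight of the Stage 3 part. A reader might infer a risk of false positives in Stage 3, but under positive correlation the opposite holds.

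**Conclusion.** The point holds within limits. As worded, the one closed behavioural item in Stage 2 cannot separate a participant vaccinated with nothing further booked from one who still refuses, and no structured doses-received item resolves this. The result can be diluted or hidden: under the assumed rates a 20-point difference shrinks to 5 points (s = 0) or 12.5 points (s = 0.5), or disappears in the third scenario. The actual size depends on uptake during follow-up and on how many vaccinated people have a next date, neither of which the article gives. The primary outcome, the Vaccine Hesitancy Index, and its analysis are not affected.

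For Stage 3, if chi-square means the ordinary test, the planned analysis ignores pairing and wastes power, with a standard error about 41% too large at an assumed correlation of 0.5. It does not produce spurious findings of benefit. ANCOVA as named does not describe how a single-group change would be estimated. Both parts should be corrected; neither undermines the RCT's main comparison.

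**What to change.** **Stage 2.** At each follow-up ask two things: whether a COVID-19 dose has been received since the last assessment, with its date, and whether a date is booked. Define the behavioural outcome as received or booked, and analyse it in the planned GEE with a logit link. Keep the scheduled-date item as a component, so that the link to the entry definition is preserved.

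**Stage 3.** For categorical outcomes name McNemar's test, or a logistic GEE over the 3-monthly contacts. For continuous outcomes name a paired analysis or a mixed model of change from baseline.

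**Cost.** One added or reworded questionnaire item and one analysis sentence. No extra visits.

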Stage 2: Participants of stage 2 will be identified from the survey population of study 1. All Hong Kong-resident adults with COVID-19 vaccine hesitancy will be eligible. People with self-reported cognitive impairments or mental disorders that might interfere with their understanding of the intervention content, and those currently engaged in another clinical trial in relation to COVID-19 vaccines, will be excluded. We calculated our sample based on sample size determination methods for repeated measures. Assuming a Type I error rate of 0.05, primary hypothesis of time x intervention interaction, a change of 1.0 as minimum difference in the mean values of the variable, and estimated correlations among repeated measure of the variable as 0.6 for T0–T1, 0.5 for T0–T2, 0.4 for T0–T3, and a statistical power of 80%, as well as 20% attrition rate, the sample size is calculated to be 168 (i.e., 84 for each group) for two study groups. Block randomisation with a size of 6 will be performed with a computer-generated list of numbers known only to an independent administrator.

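### Study 4 Stage 2: the time-by-intervention interaction, with T0 as a repeated outcome, is a valid but inefficient primary contrast; on the plan's own correlations, baseline adjustment would cut per-visit variance by 20–30%

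*Protocol article*

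**What the plan says.** In the Protocol article, section 10.2.3 (Study design, Stage 2), the sample size rests on a "primary hypothesis of time x intervention interaction, a change of 1.0 as minimum difference in the mean values of the variable", with "estimated correlations among repeated measure of the variable as 0.6 for T0–T1, 0.5 for T0–T2, 0.4 for T0–T3". It also assumes "a statistical power of 80%, as well as 20% attrition rate", and "the sample size is calculated to be 168 (i.e., 84 for each group) for two study groups". The SD of the outcome is not given. The same section describes block randomisation of individual participants.

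Section 10.2.4 (Stage 2) gives the "Primary outcome: Vaccine hesitancy measured by adult Vaccine Hesitancy Index", with assessments before and after the intervention and at 3 and 6 months. On the model it says "The generalised estimating equation will be used to analyse the effects of the intervention". Model terms, working correlation and the handling of T0 are not listed. In Study 4, ANCOVA is named only for Stage 3, which has no control group.

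**The concern.** The sample size uses correlations between T0 and each later visit, and the hypothesis is an interaction with time, so T0 enters as one of the outcomes. In a GEE with arm, time and arm-by-time, where the arms may have different T0 means, each interaction coefficient equals the difference between arms in mean change from T0.

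Randomisation makes the expected T0 means equal. The change contrast nevertheless subtracts the observed T0 difference in full. When the correlation with T0 is only 0.4 to 0.6, this adds more noise than it needs to. What is at stake is precision: the same 168 people could give a noticeably stronger primary test.

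**Working it through.** **Inputs.** From section 10.2.3: difference 1.0, alpha 0.05, power 80%, attrition 20%, 84 per arm, and T0 correlations rho of 0.6 (T1), 0.5 (T2) and 0.4 (T3). Assumed here: a two-sided test and an equal SD at every visit.

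**The plan's figure.** The attrition step fits: 134 / 0.8 = 167.5, so 168, which is 67 evaluable per arm. (140 × 1.2 = 168 fits too.) Without an SD, the 168 itself can be neither reproduced nor refuted. Solving backwards for 80% power on a change score with 67 per arm, SD = sqrt(67 / [2 × (1.96 + 0.842)² × 2(1 − rho)]). This gives 2.31 at rho 0.6, 2.07 at rho 0.5 and 1.89 at rho 0.4.

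**Variance at each visit, in units of the outcome variance.** The change score has 2(1 − rho). Adjustment for T0 has 1 − rho². Their ratio is (1 + rho)/2 and needs no SD.

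| Visit | rho | Change | Adjusted | Ratio | Reduction |
|---|---|---|---|---|---|
| T1 | 0.6 | 0.80 | 0.64 | 0.80 | 20% |
| T2 | 0.5 | 1.00 | 0.75 | 0.75 | 25% |
| T3 | 0.4 | 1.20 | 0.84 | 0.70 | 30% |

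Ignoring baseline gives 1.00, so at T3 the change score is the worst of the three.

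**Power at a visit that starts at 80%.** Power = Phi(2.802 / sqrt(ratio) − 1.96), which gives 87.9% (T1), 89.9% (T2) and 91.8% (T3). Equivalently, the evaluable total needed for 80% falls from 134 to 134 × ratio: about 108, 101 or 94.

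**One SD for all visits.** The three starting values of 80% need three different SDs. With a single SD, power at T1/T2/T3 is:

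- 80% set at T3 (SD 1.89): change 93/87/80%, adjusted 97/94/92%.
- 80% set at T2 (SD 2.07): change 88/80/72%, adjusted 94/90/86%.
- 80% set at T1 (SD 2.31): change 80/71/63%, adjusted 88/82/78%.

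**Joint 3-df test.** This needs correlations among T1 to T3, which the plan does not give; values of 0.5 to 0.7 were assumed. From a noncentral chi-square with 67 per arm, 80% on the change contrasts becomes 83–84% if the effect is at T3 only, and 92–94% if it is constant or grows linearly.

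**Check of the model form.** In one simulated complete data set (134 people, four visits), GEEs with arm, time and arm-by-time were fitted under independence and exchangeable working correlations. The interaction coefficients were 1.320, 1.222 and 1.201, the same as the raw differences in mean change.

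**The case against.** The strongest reply is that section 10.2.4 does not list the GEE terms. An article commonly leaves these to an analysis plan, and an interaction hypothesis is compatible with a model that gives both arms a common T0 mean. That stands as far as it goes: a reader might infer that the plan rules out baseline adjustment, and the document does not say so.

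It does not dispose of the point, because section 10.2.3 fixes the primary contrast. Adding T0 as a covariate while T0 stays as an outcome row gains nothing. The covariate shifts all four of a person's values equally, so within-person contrasts do not move. In complete data with independence or exchangeable working correlation, the interaction estimates and standard errors are unchanged. The contrast or the T0 constraint has to be specified.

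The second reply is that nothing is wrong with the analysis: under randomisation the difference in change is unbiased and its type I error is correct. That stands in full. This is a matter of efficiency.

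The third reply concerns size. A reader might take 88–92% as the gain for the trial as a whole, or take 94% for the joint test. Neither is supported. The first range holds visit by visit, from a separate 80% each time. The second needs an effect present at all follow-ups and correlations that are not in the document.

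**Conclusion.** The concern holds as an improvement that costs nothing, not as an error. In its standard form, the contrast fixed in section 10.2.3 has 20%, 25% and 30% more per-visit variance removable by baseline adjustment at T1, T2 and T3. These reductions rest only on the stated correlations, a common SD across visits and randomisation.

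The power gain is less certain. It is 8 to 12 points at a visit that starts at 80%, and about 4 to 15 points across visits under the three single-SD calibrations. For a joint test it is about 3 to 14 points, depending on assumed follow-up correlations and the pattern of effect. The starting 80% cannot be verified without the SD, and nothing here shows that 168 is too few.

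**What to change.** Amend the Stage 2 wording in sections 10.2.3 and 10.2.4 together, before unblinded data are seen, in one of two ways:

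- **(a)** Fit the primary GEE to the three post-baseline assessments, with the T0 Vaccine Hesitancy Index as a covariate plus arm, time and arm-by-time. Name the baseline-adjusted arm effect as the primary test, either jointly over the follow-ups or at one named visit. The arm-by-time term alone must not be the primary test: without the T0 row it asks only whether the effect differs between follow-ups, and it would miss a constant effect.
- **(b)** Keep all four assessments, use an unstructured working correlation, give both arms a common T0 mean, and test the arm-by-time terms jointly.

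In either case, report the difference in change from baseline descriptively. The cost is a few sentences: T0 is already collected, and no participants or visits are added.

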Stage 3: The ‘AI-driven Vaccine Communicator’ will be disseminated through collaborating clinicians, NGOs, community centres, and public/private healthcare providers (e.g., GPs). The five main components of the service evaluation assessment will include (1) reach—the proportion of approached participants expressing hesitancy towards COVID-19 vaccines and engaging with the programme throughout the study; (2) adoption—the proportion of participants adopting/completing the Web-based psychoeducation programme; (3) effectiveness—average outcome scores and consistent improvement in vaccine hesitancy outcomes; (4) implementation—the consistency of delivery of the programme, and effect of adaptations made to the implementation process and cost of the delivery; and (5) maintenance—the intention of the research team and participants to continue or adapt the intervention. All relevant community-based/clinical parties will be encouraged to apply our programme in their usual practice and work, our research team will trace all feedback from participants and all participants will be contacted again at 3-month intervals to assess their perceptions of and actions pertaining to COVID-19 vaccination. Stage three (the service evaluation) will consider the practical implementation of our intervention to a wider population, including its reach. Therefore, we will not limit the number of participants for stage 3 because one of the important outcomes is to ascertain how many people access and use it over the evaluation period. The estimate of minimum participant numbers for stage 3 is based on practical issues rather than statistical power to detect significant differences.

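### Study 4 Stage 3 tests effectiveness outcomes in a single uncontrolled pre-post group with ANCOVA and chi-square, which do not fit that design, and does not limit the result to description

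*Protocol article*

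**What the plan says.** Section 10.2.4 (Stage 3) declares the design openly: "We will not have a control group but will use pre-post designs as our primary focus is the practical implementation". It then gives the analysis: "The statistical analysis methods for effectiveness outcomes of stage 3 will be ANCOVA for continuous variables and Chi-square tests for categorical variables". No factor, covariate or comparison group is named.

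Section 10.2.3 (Stage 3) describes a service evaluation with five components. One of them is "effectiveness—average outcome scores and consistent improvement in vaccine hesitancy outcomes". The section sets no upper limit on participants and says the minimum number rests on practical grounds, not power. Participants are recontacted every 3 months.

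On who enters, section 10.2.1 says of Study 4 as a whole: "Our target population will be Hong Kong residents aged ≥18 who show hesitancy toward COVID-19 vaccines". A person counts as hesitant mainly "if they have no plan for a date to receive the available COVID-19 vaccines in either 1st, 2nd, or 3rd dose". People who completed three doses unwillingly and are hesitant about further ones also qualify. The Stage 3 reach measure is "the proportion of approached participants expressing hesitancy towards COVID-19 vaccines and engaging with the programme throughout the study", but section 10.2.4 also says the programme "will be disseminated to relevant stakeholders in healthcare settings and the general population to enable its use among a wider population".

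The comparative test of the same programme is the Stage 2 randomised trial against being self-informed (sections 10.1, 10.2.2 and 10.2.3).

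**The concern.** There are two linked problems.

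First, the named tests do not match the data. ANCOVA ordinarily compares groups after adjustment for a baseline covariate, and Stage 3 has one group. A standard chi-square test treats the before and after answers as independent samples, although they come from the same people. Section 7.2.3 handles the same kind of data in Study 1 with McNemar's test.

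Second, the component labelled effectiveness is read from improvement against people's own baseline. In a programme aimed at hesitant people, some average improvement may appear with no programme effect, because a group picked at a hesitant moment tends to drift back (regression to the mean). Section 4 adds that hesitancy changes over time and that motivation may follow community incidence, so secular drift can move the scores either way. The Stage 3 text addresses neither, and does not confine the result to description. Section 12 applies a p < 0.05 threshold to all analyses.

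At stake is what a favourable Stage 3 result can be said to show.

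**Working it through.** Stage 3 states no sample size, power or effect size, so there is no figure to reproduce. The checks below size the two problems.

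**1. Chi-square on paired yes/no data.** Assumptions: 200 people, correlation φ between the before and after answers, two-sided 5% test. With no change in the proportion, the paired difference has variance 2p(1−p)(1−φ)/n, while the ordinary chi-square uses 2p(1−p)/n. Its true type I error is therefore about 2[1 − Φ(1.96/√(1−φ))].

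- φ = 0.4: 1.96/√0.6 = 2.53, giving 1.1% (1.2% by simulation).
- φ = 0.5: 1.96/√0.5 = 2.77, giving 0.6% (0.6% by simulation).
- φ = 0.6: 1.96/√0.4 = 3.10, giving 0.2% (0.2% by simulation).

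For a true rise from 30% to 40%, simulated power over the same range of φ is 57% to 59% for chi-square and 77% to 92% for McNemar's test. This mismatch makes the test conservative.

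**2. ANCOVA with one group.** With baseline as the only covariate and no factor, the model has a slope and an intercept. The slope shows how follow-up depends on baseline, not whether the mean moved. With no mean change, a correlation of 0.5 and 100 people, its test rejects in about 100% of simulated runs. The intercept can be made to test mean change by taking change as the response and centring baseline. In the same null setting that test rejects in about 9% of runs, because the sampling error of the baseline mean is ignored. Neither version is specified.

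**3. Regression to the mean in the hesitancy score.** Inputs:

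- Share of the population that is hesitant: 20% (section 10.2.3, Stage 1, which says more than 20%).
- Pre-post correlations ρ: the Stage 2 planning values (section 10.2.3, "estimated correlations among repeated measure of the variable as 0.6"), falling to 0.5 and 0.4 at later visits.
- Correlation c between the entry criterion and the baseline score: not in the document, so varied here.

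The expected null improvement, in population SDs, is λ·c·(1−ρ), where λ = φ(0.842)/0.20 = 0.280/0.20 = 1.40 and φ(·) here is the normal density. The formula assumes that the entry criterion predicts the later score only through the baseline score.

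| c (assumed) | ρ = 0.6 | ρ = 0.5 | ρ = 0.4 |
|---|---|---|---|
| 1 (selected on the score itself) | 1.40 × 0.4 = 0.56 | 1.40 × 0.5 = 0.70 | 1.40 × 0.6 = 0.84 |
| 0.5 | 0.28 | 0.35 | 0.42 |
| 0.3 | 0.17 | 0.21 | 0.25 |
| 0 | 0 | 0 | 0 |

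With 200 users (illustrative) and ρ = 0.6, a two-sided 5% paired test would call an inert programme's change significant in about 100%, 99.5%, 76% and 5% of evaluations, reading down the table.

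Two variations lower these figures:

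- **Stable trait.** If the entry criterion reflects only a stable trait shared equally by both measurements, the simulated change is about 0 (0.003 SD) even though c is above zero.
- **Range restriction.** The planning correlations belong to a sample that is already hesitant. If they hold within the top 20% on the score, where the score variance is 0.219 of the population's, the implied population correlations are about 0.85, 0.78 and 0.68. The null change at c = 1 is then 0.21, 0.31 and 0.44 SD.

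**The case against.** The strongest case for the plan is that Stage 3 is openly a service evaluation. The missing control is declared with a reason, effectiveness is the standard RE-AIM label that section 12 applies to all the studies, and the causal question sits in the Stage 2 trial. A condensed article may also leave the ANCOVA factor to a fuller document: subgroups could be compared, or a repeated-measures form intended. Chi-square might loosely cover McNemar's test.

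Much of this stands. The absence of a control arm is not the defect, and no new arm is needed. What remains is that the article specifies tests for effectiveness outcomes directly after stating there are no groups, and nowhere says that the resulting change is descriptive. A subgroup comparison would not assess improvement from baseline in any case, and Study 1 shows that the protocol names McNemar's test when it means it.

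A reader might infer more than the text supports:

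- **That regression to the mean alone would make an inert programme look effective almost every time.** This requires selection on an extreme score. Entry is mainly by having no planned vaccination date, and the wording also admits general-population use. Null change may be near zero.
- **That the baseline slope is the only testable term in a one-group ANCOVA.** A centred intercept on change scores is also testable.
- **That wider uptake of the programme depends on the Stage 3 score change.** No section makes it so. Stage 3 is itself the dissemination.

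**Conclusion.** The mismatch between design and tests holds on the text alone. ANCOVA has no stated groups to compare, and an ordinary chi-square is wrong for paired answers, with a type I error of roughly 0.2% to 1.2% and reduced power in the settings checked.

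It also holds that uncontrolled improvement in Stage 3 cannot separate a programme effect from regression to the mean or secular drift. The size of the first is not determined by the document. It runs from about zero to an upper bound of 0.56 to 0.84 SD, which requires both selection on the score and Stage 2 planning correlations that apply to the whole population. Weak selection can still matter: at an assumed entry correlation of 0.3, the null shift of 0.17 SD is significant in about 76% of evaluations with 200 users. Drift cannot be quantified from the document.

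Because the randomised comparison in Stage 2 is unaffected, the severity is minor to moderate.

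**What to change.** In section 10.2.4 (Stage 3), replace ANCOVA and chi-square with methods for paired or longitudinal data in one group: GEE or a mixed model with time for continuous outcomes, and McNemar's test or GEE for binary outcomes. GEE is already the method named for Stage 2 of this study.

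In sections 10.2.3 and 10.2.4, state that Stage 3 change is reported descriptively with confidence intervals, that it does not establish a programme effect, and that effectiveness claims rest on the Stage 2 trial.

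A comparison with the Stage 2 self-informed arm may be added only as an optional exploratory analysis, labelled non-randomised. Those data are still to be collected. That arm is drawn from a telephone survey in an earlier period, while Stage 3 users come through clinicians, NGOs and community centres, so baseline adjustment would not remove the differences.

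The cost is wording only, with no added participants or visits. The downside is a more modest Stage 3 claim.
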